#### Inclusion criteria

2.2.1

Patients aged >18 years old, regardless of gender, diagnosed with CTO through coronary angiography.

Patients with evidence of myocardial ischemia who are planned to undergo or have successfully completed CTO-PCI.

Patients who can understand the purpose of the study, are willing to participate, sign the informed consent form, and are eager to follow up as required.

Patients with instruments who possess devices that measure fundamental physiological indicators (e.g., electronic blood pressure monitors).

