### Data collection and outcome measures

2.4

Eligible patients will be informed of the trial, agree to participate, and voluntarily sign the informed consent form. At the first visit, clinicians will collect basic clinical data of patients, including gender, age, medical history, and medication history. The next day, special personnel will measure patients’ height, weight, waist circumference, and resting blood pressure, and collect fasting venous blood for biochemical tests. In the data collection process, participants are assigned ID numbers, which are used as their identifiers in the system to safeguard their real identities. The collected information is stored in a highly secure database with strict access control, accessible only to the study leader and statistical experts. This ensures effective protection of participants’ privacy throughout the trial. Details of the outcome measures are shown in Table 7.

**Table 7 tab7:** Details of the outcome measures.

Outcome type	Specific content	Evaluation time	Evaluation method
Primary outcome	Evaluation of coronary microcirculation	Immediately and 1 year after revascularization	Myocardial contrast echocardiography (MCE): MBF; myocardial perfusion imaging (MPI): SDS
Secondary outcomes	Incidence of angina pectoris	1 month, 3 months, 6 months, and 12 months after revascularization	Clinical observation and recording
Secondary outcomes	Incidence of MACE during hospitalization, including all-cause death, recurrent myocardial infarction, and target lesion revascularization	Period of hospitalisation after revascularisation	Clinical observation and recording
Secondary outcomes	Incidence of 1-year MACE, including all-cause death, recurrent myocardial infarction, and target lesion revascularization	1 year after revascularization	Clinical observation and recording
Secondary outcomes	Assessment of quality of life improvement using SAQ	Period of outpatient review after discharge	Scoring with the validated Chinese version of the SAQ
Secondary outcomes	Inflammatory factors, angiogenesis-related factors, exercise-related factors	1 month, 3 months, 6 months, and 12 months after revascularization	Biochemical tests: IL-1, IL-6, and TNF; VEGF, Ang, NO, and eNOS; FSTL1 and FGF 21

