Safety outcomes	Monitoring of liver and kidney function, metabolism, and nutrition-related indicators to assess the safety of long-term use of SBP and exercise rehabilitation training	Period of outpatient review after discharge	Biochemical tests: ALT; Scr; ALB; FBG, and HbA1c; TC

MBF, myocardial blood flow; SDS, summed difference score; MACE, major adverse cardiovascular events; SAQ, Seattle angina questionnaire, SBP, Shexiang Baoxin pill, IL-l, interleukin-1, IL-6, Interleukin-6; TNF, tumor necrosis factor; VEGF, vascular endothelial growth factor; Ang, angiopoietin; NO, nitric oxide (NO); eNOS, endothelial nitric oxide synthase, FSTL1, Follistatin-like protein 1; FGF 21, fibroblast growth factor 21; ALT, alanine transaminase; Scr, serum creatinine; ALB, albumin; FBG, fasting blood glucose; HbA1c, glycated hemoglobin A1c; TC, total cholesterol.

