Patients undergoing CTO-PCI frequently have decreased intravascular pressure and coronary blood flow after the surgery; this causes the blocked vessel to appear to have a negative remodeling change, concurrently causing modifications in distal myocardial microvascular structure and function. These adverse changes interact to ultimately trigger CMVD, seriously impacting the long-term prognosis of patients (25). Consequently, accurate evaluation of coronary microvascular function, it is critical for early diagnosis of cardiovascular diseases, optimization of treatment strategies, and prediction of cardiovascular event risk. Cardiovascular magnetic resonance (CMR) imaging, covering coronary flow reserve (CFR) and index of microcirculatory resistance (IMR), widely accepted as a CMVD diagnostic criterion, is a highly promising non-invasive imaging modality of choice (26). Nevertheless, it does not display the real-time dynamic process of myocardial perfusion, and there are strict criteria for inspection equipment, so it might be challenging to perform bedside examinations on individuals who are very sick and immobile. Additionally, despite the fact that CMR can evaluate coronary microvascular function, when it comes to presenting outcomes, it lacks sensitivity and intuition. In this study, myocardial contrast echocardiography (MCE) and stress myocardial perfusion imaging (MPI) will be used as the primary outcomes to assess microvascular improvement. In recent years, these two technologies have gained prominence. Compared with conventional imaging, it provides a data-driven demonstration of myocardial blood perfusion; it also enables a more intuitive assessment of myocardial microcirculatory perfusion status, to provide a fresh method to quantify the functional state of the microvasculature accurately (27–29). Additionally, they have a close association with common outcomes like MACE; it offers a crucial basis for risk prediction and prognostic evaluation of cardiovascular disease (30). By using these technologies, physicians will formulate more accurate treatment plans to advance in cardiovascular disease diagnosis and therapy.

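### SDS, one of two primary measures, is not specific to the microcirculation, so new or treated epicardial disease between the two scans could be reported as microvascular change

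*Protocol article*

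**What the plan says.** Table 7 (section 2.4) gives the primary outcome as "Evaluation of coronary microcirculation", timed "Immediately and 1 year after revascularization", with the method "Myocardial contrast echocardiography (MCE): MBF; myocardial perfusion imaging (MPI): SDS". There are thus two primary measures. The table's footnote expands the second only as "SDS, summed difference score".

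The Discussion (section 3) states how they are to be read: MCE and "stress myocardial perfusion imaging (MPI) will be used as the primary outcomes to assess microvascular improvement".

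The population is set in section 2.2.1: "Patients with evidence of myocardial ischemia who are planned to undergo or have successfully completed CTO-PCI". Neither this list nor the exclusions in section 2.2.2 require complete revascularization or the absence of other epicardial lesions. Absence of remaining ischemia appears only in Table 3, as a characteristic of patients in the moderate exercise grade.

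Table 7 also defines MACE at 1 year as "all-cause death, recurrent myocardial infarction, and target lesion revascularization".

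**The concern.** A summed difference score adds up how much worse perfusion is under stress than at rest. A narrowed epicardial artery can produce such a defect, and so can a diseased microvascular bed. The score alone does not tell them apart, yet the plan attaches a microvascular label to it.

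What is at stake is the attribution of the main result. Suppose one arm has less restenosis, less progression in another vessel, or a different rate of repeat revascularization before the 1-year scan. Its SDS would then differ for epicardial reasons, and the trial would report better or worse microcirculation. The direction cannot be predicted. Fewer stent failures would improve SDS, but a repeat procedure before the scan could also lower SDS in a patient whose stent had failed. The Background looks ahead to guideline recommendations on managing microvascular dysfunction, so the attribution carries much of the trial's claim.

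**Working it through.** The plan has no figure to reproduce. Section 2.9 gives a sample-size formula but no means, SDs or N. The check sets the text side by side and then traces what the two scans can and cannot remove.

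**1. Label against measure.** The label is coronary microcirculation (Table 7) and microvascular improvement (Discussion). One of the two measures is a stress-minus-rest perfusion score. No stated element of the article turns that score into a microvascular one: it gives no patency check at 1 year and no entry rule on other lesions.

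**2. What the two scans remove.** Write a patient's SDS as a microvascular part m plus an epicardial part c.

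- Stable lesion, same c at both scans: change = (m₁ + c) − (m₀ + c) = m₁ − m₀. The lesion cancels.
- New epicardial defect of size d by 1 year: change = (m₁ − m₀) + d.
- Epicardial lesion of size d treated between the scans: change = (m₁ − m₀) − d.

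Only new, changed or treated epicardial disease is therefore mistaken for microvascular change. This assumes that the immediate scan is used as a baseline, which the article does not state, and that it precedes any material treatment effect.

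**3. Does this differ between arms?** If the net share of patients with such a change differs between two arms by Δf, and each such patient moves by e within-arm SDs, the contrast shifts by Δf × e. Randomization makes Δf zero on average unless treatment affects epicardial disease. The protocol expects that it may. The Background says the pill dilates coronary arteries, stabilizes plaques and slows atherosclerosis, and it hypothesizes fewer MACE within a year. Two of the three MACE components, recurrent infarction and target lesion revascularization, are commonly epicardial events.

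**4. Illustration.** All inputs are assumed, because the documents give no rate and no SD.

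| Δf | e = 1 | e = 2 | e = 3 |
|---|---|---|---|
| 0.02 | 0.02 SD | 0.04 SD | 0.06 SD |
| 0.05 | 0.05 SD | 0.10 SD | 0.15 SD |
| 0.10 | 0.10 SD | 0.20 SD | 0.30 SD |

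For example, 0.05 × 2 = 0.10 SD. The shift is negligible at one corner of the table and could matter at the other.

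**The case against.** **SDS is not the whole outcome.** MBF by MCE is also primary. This stands. The argument above is worked for SDS. For MBF one can say only that the article states no patency rule for it either.

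**The choice was argued.** The sentence in the Discussion that calls CFR and IMR accepted criteria for microvascular dysfunction is about cardiac magnetic resonance. The authors then give reasons for preferring MCE and MPI, such as real-time display and bedside use. That justifies the techniques. It does not make SDS specific to the microvasculature.

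**Details may sit elsewhere.** Segment definitions and the handling of later revascularization are often left to an analysis plan or imaging manual, neither of which is shown. Their absence is not the point here. The point is that the stated label goes further than the stated measure.

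**Randomization protects the comparison.** It largely does. A difference that arises because treatment altered epicardial disease is a real treatment effect. What is wrong is its name.

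Three stronger readings are tempting, and the documents do not support them:

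- A reader might infer that SDS here counts ischemia from any vessel and any cause. The article does not say whether the score is global or limited to the CTO territory.
- A reader might infer that untreated lesions are scored as microvascular change. A stable lesion appears on both scans and would largely cancel if the immediate scan serves as baseline.
- A reader might multiply the sample size for epicardial noise. No SD or lesion rate is given, and section 2.9 takes the variance from pilot studies, which would already contain that noise if they measure the same outcome in the same kind of patient.

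**Conclusion.** The concern holds as a problem of attribution. SDS, one of two primary measures, is not specific to the microcirculation, and Table 7 with the Discussion treats a change in it as microvascular improvement. Entry leaves room for residual and non-CTO epicardial disease, target lesion events are anticipated, and the protocol's own hypotheses give a route by which epicardial change could differ between arms.

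The size cannot be stated from the documents. The illustrative shift of 0.02 to 0.30 SD depends wholly on assumed shares and defect sizes. It is not evidence that bias is present. The conclusion rests on two things: the general property that a stress-minus-rest score does not identify the cause of a defect, and the absence from the article of anything that would rule out an epicardial cause. It should be settled before the result is worded, and preferably before pilot data fix the SD.

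**What to change.** - **Primary analysis:** adjust the 1-year values of both measures for the immediate post-PCI scan and for residual epicardial stenosis recorded from the index angiogram.
- **Sensitivity analysis:** prespecify one that accounts for patients with known restenosis, re-occlusion or revascularization before the 1-year scan. These events follow randomization, and the article describes no routine follow-up angiography, so the analysis will capture only detected cases and should be read as supportive.
- **CTO-territory analysis:** report it as supportive only. Making it primary would discard possible effects of systemic treatments elsewhere and would still leave restenosis of the treated vessel in the score.
- **Wording:** state the primary conclusion as myocardial perfusion, not coronary microcirculation, unless epicardial causes have been ruled out.

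**Cost:** a narrower claim and slightly more analysis work. No new procedure is needed, because both scans are already scheduled and entry already requires coronary angiography. Residual stenosis would have to be extracted from that angiogram if it is not already recorded.

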**Methods:**

This prospective, single-center, randomized controlled trial involves CTO-PCI patients divided into four groups: Shexiang Baoxin pill, exercise rehabilitation, combined, and control. The exercise protocol includes pre-assessment, a three-phase prescription, CPET-based intensity grading, various exercise methods, remote monitoring, and quality control. The primary outcome is coronary microcirculation assessed by myocardial contrast echocardiography and stress myocardial perfusion imaging 1-year post-surgery. Secondary outcomes include angina incidence, major adverse cardiovascular events (MACE), quality-of-life improvements, and mechanism-related biological indicators, with safety outcomes monitoring liver and kidney function. Data will be analyzed statistically.

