### Study design

2.1

This study is a prospective, single-center, randomized controlled clinical trial. Patients with CTO who underwent PCI in the cardiology department of our hospital. Using a computer-generated block randomization sequence (block size = 4), participants were allocated in a 1:1:1:1 ratio to one of four parallel groups: the SBP group, the exercise rehabilitation group, the combined SBP and exercise rehabilitation group, and the control group. Allocation concealment was ensured by a central randomisation module embedded in the Hospital Information System (HIS); the treatment assignment was automatically released only after the participant had been registered and baseline data entry was completed. Figure 1 shows the details of the study process. This study will strictly adhere to the Standard Protocol Items: Recommendations for Interventional Trials (SPIRIT) reporting standard (20).

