### Statistical analysis

2.9

In this study, there is currently insufficient reference data based on the primary outcome to support sample size calculations; therefore, pilot studies are being conducted to obtain the key parameters required for the formula:

$$n=\varphi^{2}(\sum S_{i}^{2}/g)/[\sum {\left({\bar{X}}_{i}-\bar{X}\right)}^{2}/(g-1)]$$

(where the formula parameter *g* = 4, representing a total of 4 groups in the study) to estimate the required sample size scientifically and accurately, with the significance level set as two-tailed *α* = 0.05, the statistical power set as 1-*β* = 90% (*β* = 0.1), and after calculating the theoretical sample size for each group using the formula upon completion of the pilot studies, a 20% dropout rate will be considered to adjust the theoretical sample size to obtain the final sample size for each group, with the total sample size of the study being the final sample size of each group multiplied by 4.

Statistical analyses will be conducted using appropriate methodologies based on the data characteristics. Continuous variables will be reported as means ± standard deviations, while categorical variables will be presented as frequencies and percentages. Group differences will be assessed using t-tests, analysis of variance (ANOVA), or chi-square tests, as appropriate. A *p*-value of less than 0.05 will be considered indicative of statistical significance. All statistical analyses will be conducted using software such as SPSSAU.

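### Two measures are primary, with no rule on whether one or both must succeed or which contrast decides; if either counts, the false-positive chance is about 8–10% even with one ANOVA each (correlation 0.8 to 0)

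*Protocol article*

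**What the plan says.** - **Primary outcome.** Section 2.4, Table 7, has a single primary row, coronary microcirculation, evaluated by "Myocardial contrast echocardiography (MCE): MBF; myocardial perfusion imaging (MPI): SDS". The Abstract uses the singular: "The primary outcome is coronary microcirculation assessed by myocardial contrast echocardiography and stress myocardial perfusion imaging 1-year post-surgery". The Discussion uses the plural: "myocardial contrast echocardiography (MCE) and stress myocardial perfusion imaging (MPI) will be used as the primary outcomes to assess microvascular improvement".
- **Arms.** Section 2.1: "participants were allocated in a 1:1:1:1 ratio to one of four parallel groups".
- **Tests.** Section 2.9: "Group differences will be assessed using t-tests, analysis of variance (ANOVA), or chi-square tests, as appropriate". No contrast is named as primary.
- **Decision rule.** Section 2.9: a p "value of less than 0.05 will be considered indicative of statistical significance". This is the only rule given.
- **Sample size.** Section 2.9 sets two-tailed alpha 0.05, power 90% and a formula for four groups (g = 4) that takes one set of group means and SDs. No N is given, because "there is currently insufficient reference data based on the primary outcome to support sample size calculations"; pilot studies are to supply the parameters.

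**The concern.** The two measures come from different imaging methods and can disagree. The article defines no composite, no order between them and no requirement that both succeed. A result that is positive on MBF and null on SDS, or the reverse, therefore has no agreed conclusion. If the sponsor may claim success on whichever measure, and whichever pair of arms, falls below 0.05, the real false-positive rate for the primary claim is above the stated 5%.

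The gap also affects sizing. The formula needs the means and SDs of one outcome, and the article does not say which of the two measures will supply them.

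**Working it through.** **Inputs from the article.** Two primary measures (Table 7); four equal arms (section 2.1), hence 4 × 3 / 2 = 6 pairs, or 3 contrasts with any one reference arm; two-tailed alpha 0.05 (section 2.9).

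**Assumptions not in the article.** Success on either measure counts, except where stated. The correlation between the measures is unknown and is varied from 0 to 1; its sign does not matter, because the tests are two-sided. All arms are equal on both measures, and arm means are treated as normal (large sample), since no N is given. The 1-year value is the one tested.

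**Step 1, the plan's own level.** One ANOVA on one measure gives 5.0%, as stated.

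**Step 2, one ANOVA per measure.** For independent measures: 1 − 0.95² = 9.75%.

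**Step 3, three contrasts with one reference arm.** The contrasts share that arm, so they are not independent. Simulation gives 12.5% (0.1254) on one measure. For two independent measures: 1 − (1 − 0.1254)² = 23.5%.

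**Step 4, all six pairs.** On one measure, the probability that the studentized range of four groups exceeds √2 × 1.96 is 20.3%. For two independent measures: 1 − (1 − 0.2033)² = 36.5%. Treating the 12 tests as independent would give 1 − 0.95¹² = 46%, which is too high because pairs share arms.

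**Step 5, correlated measures.** Simulation with 1,000,000 replicates of four arm means on two measures. The ANOVA criterion is Σ(Xᵢ − X̄)² above the 95% point of chi-square with 3 df; the pairwise criterion is |Xᵢ − Xⱼ|/√2 > 1.96. At correlation 0, three cells use the exact values: 9.75% and 36.5% from steps 2 and 4, and 0.05² = 0.25% for both required.

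| Rule | corr. 0 | 0.5 | 0.8 | 0.9 | 1 |
|---|---|---|---|---|---|
| One ANOVA each, either counts | 9.75% | 9.2% | 8.0% | 7.2% | 5.0% |
| Three contrasts each, either counts | 23.5% | 22.0% | 19.1% | 17.2% | 12.5% |
| Six pairs each, either counts | 36.5% | 34.0% | 29.6% | 27.1% | 20.3% |
| One ANOVA each, both required | 0.25% | 0.8% | 2.1% | 2.8% | 5.0% |

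**Step 6, two variants.** If pairwise tests follow only a significant ANOVA on the same measure, the either-measure error with all arms equal is about that of the first row (9.7% at correlation 0, 8.0% at 0.8). Requiring both measures protects the 5% only with one test each: if any of the six unadjusted pairs may be positive on both, the error is 4.7% at correlation 0.5, 6.1% at 0.6 and 10.2% at 0.8.

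**The case against.** The strongest reply is that the article does not commit to the liberal scheme. The Abstract's singular outcome, assessed by one method and the other, can be read as requiring both; with one test each, that inflates nothing. The g = 4 formula points to an overall four-group test, and with that gate the error stays below 10% when all arms are equal. The stated aim concerns the combined treatment, which suggests at most three contrasts rather than six. Adjustment of follow-up contrasts is commonly left to an SAP, which is not shown.

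Most of this stands. A reader might infer that the plan's error rate is 36.5%, or that it prescribes all six unadjusted pairwise tests on both measures. The text supports neither: it has one general sentence on significance and a list of tests to be used as appropriate. The formula's single-outcome form is not an error either, since it can be applied to each measure and the larger n taken.

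A reader might also infer that SDS is unsuited to means and t-tests because its values pile up at a floor, or that the many biomarker tests add to the problem. The article gives no range or distribution for SDS. The biomarkers are secondary, no testing scheme for them is fixed, and they do not enter the primary error rate.

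What the reply does not remove is the missing success rule. Which measure is primary, and whether one or both must succeed, belongs in the protocol. This article moves between singular and plural and does not decide.

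**Conclusion.** The point holds as a conditional one. Two measures are primary, p below 0.05 is the only rule, and neither the one-or-both question nor the deciding contrast is settled.

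- **Either measure, one ANOVA each:** about 8–10% for correlations from 0.8 down to 0, falling to 5% at correlation 1.
- **Either measure, three unadjusted contrasts with one reference arm:** about 19–24% over the same correlations.
- **Either measure, all six unadjusted pairs:** about 30–36.5%. This is the worst case the wording leaves open, not the plan's stated procedure.
- **Both measures required, one test each:** at most 5%.

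The spread, from under 1% to above 36%, shows how far the error rate depends on choices that the article leaves open. It should be corrected before N is set, because the choice also determines what enters the sample-size formula.

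**What to change.** Before the pilot-based sample size is computed:

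1. Name one of the two measures at 1 year as the primary outcome and use its means and SDs in the formula.
2. Test it first with the four-group test that the formula sizes for, at two-sided 0.05. Follow with pairwise contrasts under a stated familywise adjustment. The adjustment is needed because the overall test protects these contrasts only when all four arms are equal.
3. Make the other measure a key secondary, tested only if the primary is significant.
4. Use the same singular wording in the Abstract, Table 7 and the Discussion.

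Alternatively, state that both measures must be significant, with one named test each, and take the larger of the two sample sizes.

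**Cost.** Under the first option, a positive result on the second measure alone is no longer trial success, and adjusted pairwise contrasts have somewhat less power. The second option lowers power or raises n: sizing each measure at 90% and taking the larger n guarantees joint power of only 1 − 0.10 − 0.10 = 80% (0.90 × 0.90 = 81% if the measures are independent and each has exactly 90%). To guarantee 90% jointly, size each at 95%, since 1 − 0.05 − 0.05 = 90%.

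For comparison, keeping either-measure success by splitting alpha to 0.025 per measure needs about 16% more patients for the ANOVA (noncentrality 16.42 / 14.17 = 1.16).
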